### General stress

In order to assess a participant’s stress levels on each test day, a short questionnaire will be completed at the beginning of each session. High stress may increase craving for substances [43, 44], and this questionnaire will allow for this factor to be considered as a covariate. The Perceived Stress Scale will be used to measure the degree to which situations in one’s life are appraised as stressful [45]. It consists of 10 items, each of which can be rated between 0 and 4 on a Likert-type scale, assessing the perceived stress of each participant over the past 4 weeks. Items are summed to generate a single score of between 0 and 40, with higher scores indicating greater perceived stress. The 10-item version of the Perceived Stress Scale is widely reported as having good internal consistency and validity [46].

### Inhibitory control

For the assessment of inhibitory control, a computer-based version of the Stroop test is administered with E-Prime 2.0 (PST, USA). During the task, participants are presented with a colour word appearing in the same colour (e.g. “blue” printed in blue) on compatible trials or in a different colour (e.g. “blue” printed in green) on incompatible trials. While the word meaning has to be ignored, participants are instructed to press a key corresponding to the ink colour. The conflict resulting from the presentation of the relevant and irrelevant dimensions of the stimuli challenges the attentional system. In this respect, a system that efficiently suppresses task-irrelevant dimensions allows fewer conflicts between the colour word and the ink colour. This indicates greater efficiency of the inhibitory control system. Similar to the original Stroop paradigm, computerised versions of this task have been found to elicit interference effects and to have a high reliability [47].

In the present study, participants complete 12 practice trials, followed by four test blocks with 54 trials each. Sufficient practice rounds are included to reduce learning effects. In each test block, only compatible or incompatible trials are presented to allow the detection of interference effects using fNIRS. The blocks are alternated and the trial type employed in the first block is counterbalanced across participants. Between blocks there is a 30-s fixation period, which allows HbO_2_ concentrations to return to baseline. During each trial, the stimuli are presented over 2000 ms or until a response is collected. The inter-stimulus interval is varied randomly between 200 and 400 ms to avoid guessing.

The different colour words were presented with equal probability across all trials. For the assessment of task performance, the accuracy and reaction time (on response-correct trials) are calculated for incompatible trials.

### Alcohol or cocaine cue exposure

Alcohol-dependent participants will be asked to report the type of alcohol (wine, beer, schnapps) which they chiefly consume or prefer. It has been established that, in research involving substance cues, craving is more reliably elicited by cues specific to the individual and their consumption history, and is consequently not a reaction to arousing cues in general [48]. Cocaine-dependent participants will not undergo this step, as there is no variation in the substance itself. All participants will be shown a block of six 1-min films, alternating cocaine cues or alcohol cues (of the preferred substance) with neutral cues. Neutral cues have to be included to be able to associate changes in HbO_2_ with craving rather than visual processing alone. Each 1-min film is separated from the next by a 30-s fixation period, which allows HbO_2_ concentrations to return to baseline. The same film block will be shown at every time point (specifically, prior to and after every condition, for each of the three conditions) in order to ensure that there is no variation in the emotional intensity of the cue.

Each 1-min film is designed to replicate activities carried out in a real-life setting. In order to achieve this, the films are created with a small camera strapped to the head, so that the viewer sees everything from the perspective on the camera holder and can see their hands picking up objects, etc. In the alcohol-cue films, the camera holder walks through a supermarket, arrives at the aisle selling the preferred beverage of the participants, looks at the bottles, picks some up and finally puts some in a basket before moving on. In the neutral films shown following the alcohol films, this sequence is repeated but some type of cleaning product is the examined and chosen. In the cocaine-cue films, the camera holder walks to a flat surface, takes out a small bag of cocaine and begins to snort it or prepares it in lines. The neutral cues are filmed in the same environment, but another activity (making tea, writing, opening a book) is undertaken on the flat surface.

Prior to the study start, the films will be tested on 10 alcohol-dependent and 10 cocaine-dependent individuals (who will not later take part in the study) in order to ensure that the film reliably elicits craving.

### Craving self-report

Current craving levels will be assessed using the Alcohol Craving Questionnaire—Short Form [49] or the Cocaine Craving Questionnaire—Brief [50]. The Alcohol Craving Questionnaire—Short Form consists of 12 questions rated on a 7-point Likert-type scale, addressing the degree to which craving is experienced by the respondent in the current moment. A general craving score is generated by summing the scores of each item (three items are reverse-scored) to produce a score between 12 and 84, with higher scores indicating greater craving. The Short Form has been shown to have good levels of reliability [51] and internal consistency [52]. The Cocaine Craving Questionnaire—Brief consists of 10 items which assess current levels of craving for cocaine. The respondent rates each item on a 7-point Likert-type scale and scores are summed to produce a final value ranging between 7 and 70, with higher scores indicative of greater craving. The questionnaire is reported to have good reliability and internal consistency [53].

### fNIRS recordings

Using fNIRS (NIRSport, NIRx Medizintechnik GmbH, Germany), cerebral oxygenation is recorded during the inhibitory control task and alcohol cue exposure. Probes are applied using a flexible cap adjustable to the participant’s head size. Light sources and detectors are placed over the prefrontal region using the Fz position of the EEG as reference. Channel distances are fixed to 35 mm to allow measurements at equal depths. Offline processing of the collected data is performed with Homer 2 [54] and includes the following steps: removal of discontinuities, artefact rejection and correction using spline interpolation, band-pass filtering (0.01–0.2 Hz), conversion into haemodynamic states using the modified Beer–Lambert Law [55] and normalisation using the pre-task period as baseline. As findings of a review have indicated widespread prefrontal cortex hypoactivation during inhibitory control tasks and hyperactivation during the presentation of drug-related cues, cerebral oxygenation is examined across channels placed over the prefrontal region [7].

HbO_2_ is calculated as the dependent variable, because Strangman et al. [56] have shown high correlations between this parameter and the blood oxygen level. For the assessment of cue-elicited craving, difference waveforms (created by subtracting the haemodynamic response to neutral cues from alcohol/cocaine cues) are extracted for statistical analysis.

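### The 0.01 Hz high-pass filter lies above the rate at which cue and neutral films alternate, so it suppresses much of a sustained cue-minus-neutral HbO2 contrast, a primary outcome

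*Protocol article*

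**What the plan says.** **Filter.** In the protocol article, fNIRS recordings, the offline steps include "band-pass filtering (0.01–0.2 Hz"), followed by normalisation to the period before the task. Filter type and order are not given, nor whether that baseline precedes the whole task or each block.

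**Films.** Under Alcohol or cocaine cue exposure: "All participants will be shown a block of six 1-min films, alternating cocaine cues or alcohol cues" with neutral ones, and "Each 1-min film is separated from the next by a 30-s fixation period". The endpoint is a subtraction: "difference waveforms (created by subtracting the haemodynamic response to neutral cues from alcohol/cocaine cues) are extracted for statistical analysis" (fNIRS recordings, repeated in Statistics). The Abstract lists the haemodynamic response to the film among the primary outcomes.

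**Stroop.** Under Inhibitory control, there are "four test blocks with 54 trials each", with block types alternating. "Between blocks there is a 30-s fixation period", and in each trial "the stimuli are presented over 2000 ms or until a response is collected", followed by an interval of 200 to 400 ms. The Statistics section analyses the HbO2 response to incompatible trials alongside reaction time.

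**The concern.** A high-pass filter removes variation slower than its cut-off. If the contrast to be measured itself repeats more slowly than that, the filter treats it as drift. The film timings and the cut-off are both stated, and they conflict. The neutral films are there to separate craving from visual processing. The filter works against this: it tends to pass the on/off response shared by both film types and to suppress the part in which they differ. With 20 participants per group planned, a null result on film HbO2 would be hard to interpret.

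A second effect concerns the Stroop test. Each trial ends at the response, so a block is longer in a slower participant, and a longer block loses more to the same filter. Filtered HbO2 is then partly tied to reaction time, which is itself an outcome.

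**Working it through.** The plan states no retained-signal figure, so there is none to reproduce. The frequencies follow from the stated timings; the retained fractions need assumptions, given below.

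**Film frequencies**
- One film plus gap: 60 + 30 = 90 s, or 1/90 = 0.0111 Hz.
- One cue-neutral cycle: 2 × 90 = 180 s, or 1/180 = 0.0056 Hz, below 0.01 Hz.
- Take the contrast as +1 for 60 s, 0 for 30 s, −1 for 60 s, 0 for 30 s. Its fundamental has amplitude (4/π) × sin(π/3) = 1.103 and power 1.103²/2 = 0.608. Total power is 120/180 = 0.667, so 0.608/0.667 = 91% of the power sits at 0.0056 Hz. The third harmonic is zero, because sin(3π/3) = 0.

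**Filter gain at 0.0056 Hz**
- A single-pass Butterworth high-pass of order n has gain 1/√(1 + (0.01/0.00556)^(2n)). Zero-phase filtering squares it, giving 1/(1 + 1.8^(2n)).
- Order 1: 1/(1 + 3.24) = 0.24.
- Order 3: 1/(1 + 34.0) = 0.03.
- Order 5: 1/(1 + 357) = 0.003.

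**Film contrast retained.** Simulation of six films. Assumptions: a response sustained over the film, a double-gamma haemodynamic response, 60 s of rest before and after.

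| Cut-off and filter | Baseline | Retained |
|---|---|---|
| 0.01 Hz, zero-phase Butterworth or brick wall | none or pre-task | 3–30% |
| 0.01 Hz, same filters | pre-block | 28–47% |
| 0.01 Hz, single-pass, orders 1–5 | any | −12% to 55% |
| 0.003 Hz, zero-phase Butterworth, orders 1–5 | pre-task or pre-block | about 75–95% |

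For zero-phase Butterworth filters alone, repeated runs with slightly different settings put the 0.01 Hz result at about 5–45%. More than half was kept in only one variant (single-pass, order 1, early averaging window).

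**Stroop block/rest cycle.** Length = 54 × (RT + 0.3) + 30 s, where RT is mean reaction time in seconds and 0.3 s is the mean inter-stimulus interval. The RT values are illustrative; the article gives none.
- RT 0.6 s: 48.6 + 30 = 78.6 s, or 0.0127 Hz.
- RT 1.0 s: 70.2 + 30 = 100.2 s, or 0.0100 Hz.
- RT 1.2 s: 81 + 30 = 111 s, or 0.0090 Hz.

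The cycle therefore crosses the cut-off at an RT of about 1.0 s.

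**Planned Stroop variable.** Incompatible response, true value fixed, order 3 zero-phase:

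| Cut-off | Baseline | RT 0.6 s | RT 0.7 s | RT 1.0 s |
|---|---|---|---|---|
| 0.01 Hz | pre-task | 0.658 | 0.620 | 0.512 |
| 0.01 Hz | pre-block | 0.784 | 0.735 | 0.600 |
| 0.003 Hz | pre-task | 0.764 | 0.748 | 0.717 |
| 0.003 Hz | pre-block | 0.999 | 0.996 | 0.988 |

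- At 0.01 Hz, from RT 0.6 to 0.7 s: 1 − 0.620/0.658 = 5.8% and 1 − 0.735/0.784 = 6.3%. Across orders 1 to 5 the fall is about 3–10% per 100 ms.
- At 0.003 Hz, from RT 0.6 to 1.0 s: 1 − 0.717/0.764 = 6.2% over 400 ms with a pre-task baseline, but only 1 − 0.988/0.999 = 1.1% with a pre-block baseline.

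**The case against.** **Film figures rest on unstated choices.** Filter order and type, baseline, averaging window and response shape are all open. The alcohol film begins with a walk through a supermarket that the neutral film shares, so the cue-specific response need not fill 60 s. A 15-s onset response keeps about 64–92%; a response running from 20 to 60 s keeps only 12–36%. This stands as a limit on the size of the loss. It does not reconcile the cut-off with the film timing.

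**Attenuation is not lost power.** A reader might infer that a contrast measured at a fraction of its size costs power in proportion. An ANOVA depends on signal relative to noise, and the filter also removes slow noise. With 1/f noise (exponent 0.5–2) plus 0.1 Hz waves, the signal-to-noise gain at 0.003 Hz ran from 13% to about twofold. The objection stands: the gain is real, but its size is uncertain.

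**The Stroop test is less affected.** A reader might infer that most of the Stroop signal is lost too, because block types alternate below 0.01 Hz and the article separates them with this aim: "In each test block, only compatible or incompatible trials are presented to allow the detection of interference effects using fNIRS". But Statistics analyses the incompatible response, not the difference between block types. For RT 0.6–1.0 s that variable kept about 32–71% with a pre-task and 58–90% with a pre-block baseline. Partial attenuation is the right description.

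**Reaction-time link.** A reader might also infer that the filter would imitate the predicted rise in prefrontal activity after moderate exercise, or create false patient-control differences. The article gives no reaction-time shift or group gap to support that. At about 6% per 100 ms, a 30–50 ms change moves HbO2 by about 2–3%. The hypotheses compare conditions within patients, so a stable group gap does not by itself bias them.

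**Conclusion.** The conflict is real and follows from the article's own timings: the cue-neutral cycle is 0.0056 Hz and the high-pass cut-off is 0.01 Hz. For a sustained response and a zero-phase Butterworth filter of order 1–5, the film HbO2 contrast keeps about 5–45% of its size, against about 75–95% at 0.003 Hz. The loss is smaller for a brief onset response.

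The Stroop link to reaction time is secondary: a modest artefact tied to another outcome, and not evidence that a Stroop HbO2 finding would be spurious. Self-reported craving, Stroop accuracy and reaction time are untouched. This should be fixed, mainly for the film HbO2 outcome.

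**What to change.** Replace the 0.01 Hz high-pass with a general linear model that has regressors for cue and neutral films (and compatible and incompatible blocks) of their actual duration, plus slow-drift terms. As a minimum, lower the cut-off to about 0.003 Hz and use a pre-block baseline; with a single pre-task baseline, 0.003 Hz reduces the reaction-time link without removing it. Keep the 0.2 Hz low-pass. State the filter type, order and baseline period.

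The cost is offline processing only. The article describes the trial as ongoing, so recordings already made should be reprocessed in the same way; no new data are needed. The downside is that more slow drift stays in the signal and has to be modelled.

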### Experimental conditions

To estimate the maximal heart rate of each participant, the algorithm 211 – (0.64 × age) will be used [57].

All participants will undergo three conditions, on three separate days, in a counterbalanced order. The days on which participants participate will be separated by 2–4 days. All sessions will take place in the same laboratory room at the Department of Sport, Exercise and Health at the University of Basel. Trained members of the investigative team will oversee all conditions. Owing to the nature of the intervention, investigators will not be blinded to the conditions.

The reading condition serves as a resting state comparison. Subjects will be asked to read an article about architecture in Basel. The article is 13 pages long, excluding references.

The moderate exercise condition requires participants to train on a cycle ergometer at between 50 and 60% of their maximal heart rate. Participants will wear a heart rate monitor, which will be constantly observed by study personnel, to ensure that they exercise with the correct intensity. If the participant exceeds or fails to meet the appropriate intensity, prompts will be given. Prompts will not be recorded. This constitutes a moderate, aerobic exercise bout. The exercise will last 20 min.

The intensive exercise condition is identical to the moderate condition, but participants will exercise at a pulse of between 70 and 80% of their maximal heart rate, constituting a bout approximately at the anaerobic threshold.

### Statistics

Sample size is calculated a priori using G*Power 3.1 [58]. Based on effect sizes reported in previous studies [25, 40] and an alpha level set to 0.05, the initial power analysis indicates that 17 participants per group are required to reach 85% statistical power. As drop-outs have to be expected, the sample size is increased to 20 participants per group. Note that the power analysis is based on the acute effects of moderate aerobic exercise on prefrontal cortex activity and inhibitory control. The statistical analysis of collected data is performed with SPSS 23.0 (IBM Statistics, USA) for Windows. Acute effects of exercise on inhibitory control and HbO_2_ concentration are examined using a 2 (group: alcohol dependent, healthy controls) × 3 (condition: control, moderate exercise, highly intense exercise) × 2 (time: pre, post) ANOVA on reaction time and the haemodynamic response to incompatible trials of the Stroop colour–word test. Additionally, effects of exercise on cue-elicited craving and HbO_2_ concentration (neutral cues subtracted from alcohol/cocaine cues) are investigated by applying a 2 (group) × 3 (condition) × 2 (time) ANOVA. Main effects and interactions are reported. Subsequently, Bonferroni-corrected *t* tests are used to decompose any significant interactions. The level of statistical significance is set to *p* < 0.05. Data from participants who do not complete all three measurement points will not be used.

Regarding missing data, as participants who do not complete all three sessions will be excluded from the study, it is anticipated that missing data will chiefly be due to faults in the fNIRS and Stroop programming, and thus will be missing at random. For this reason, multiple imputation will be used to address this issue.

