In summary, there is evidence that craving in alcohol or cocaine-dependent individuals can be reliably elicited by exposure to images, and that craving correlates with specific activation patterns in regions of the prefrontal cortex. The activation of these regions can be imaged using fNIRS. Inhibitory control may moderate craving, and activation during inhibitory control tasks can also be imaged using fNIRS. Finally, during an acute bout of exercise, activity in the prefrontal cortex increases (at moderate intensities) and decreases (at high intensities), and acute exercise has been shown to influence both inhibitory control and craving. While the evidence for exercise in general is weaker for alcohol than for cocaine dependence, the single study to date to examine the effects of acute bouts on craving found reductions for both substances. Consequently, the aim of this study is to examine whether, following acute exercise bouts at moderate and high intensities, reduced craving and increased inhibitory control can be observed in alcohol or cocaine-dependent individuals. As the focus of this study is the potential of exercise to be integrated into treatment, individuals in treatment for their dependence, who have been abstinent for a short period, will be recruited.

Based on the state of research to date, we propose the following hypotheses:In alcohol-dependent and cocaine-dependent participants, compared to a passive control condition, a bout of moderate exercise will:reduce self-reported craving;improve behavioural performance on the Stroop test;elicit increased activity in the prefrontal cortex during the Stroop test; andbe followed by decreased activity in the prefrontal cortex during exposure to substance-related cues.

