### Study design

This study is a randomised controlled trial involving three conditions: moderate exercise, intense exercise, and rest. Alcohol-dependent, cocaine-dependent and healthy control subjects will undergo all three conditions in randomised order. The order will be determined using a computer-generated ordering system. The random sequence was generated by the web-based Research Randomizer (randomizer.org), which yielded 60 permutations of the order of sessions (rest, moderate exercise, intense exercise). These permutations were printed, placed in separate envelopes and given to a colleague not involved in the study to distribute upon recruitment of each participant. Due to the nature of the intervention, blinding will not take place. The funder has no role in the design, analysis or interpretation of the study.

No data monitoring committee is involved in this study as the intervention (exercise) is not untested or high risk, and as only two acute sessions are involved any adverse events will be addressed immediately by the investigative team. The study therefore meets the criteria of “non-critical indications where patients are treated for a relatively short time and the drugs [in this case, exercise] under investigation are well characterized and known for not harming patients” [41].

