### Participants

Twenty alcohol-dependent, 20 cocaine-dependent and 20 healthy control individuals will be recruited to take part in the study (for power calculation, please see “Statistics”). Patients from the inpatient and outpatient branches of the clinic will be informed about the study by physicians, fliers and, in the case of the inpatient clinic, periodic visits from the investigators. All individuals receiving treatment for one of the substance use disorders in question will be approached, in order to ensure that as many individuals as possible who fit the inclusion criteria are reached. The mean age and gender distribution of the cocaine-dependent and alcohol-dependent participants combined will be used as a guide for finding matched healthy controls. Alcohol-dependent and cocaine-dependent individuals will be recruited from the University Psychiatric Clinic of the University of Basel.

Inclusion criteria for these individuals are: age between 18 and 75 years; meeting three or more of the DSM-IV criteria for substance dependence (as determined by the treating physician); minimum of 20 days and maximum of 40 days abstinence from substance of dependence; able to understand and complete the informed consent; able to travel to study site independently, as confirmed by the treating psychiatrist; assessed for physical and mental fitness by the treating physician; and cleared to take part in the study.

The healthy control group will be recruited through personal contacts (the friends and family members of the investigative team and other employees of the Department for Sport, Exercise and Health) and matched for age and gender. Inclusion criteria for the healthy control group are: age between 18 and 75 years; fewer than 3 h of physical exercise or sport per week; and no history of problematic alcohol or illicit drug consumption. All participants will receive a written document outlining the requirements of the study, and informing them that withdrawal at any point will not adversely affect their medical treatment. Participants who agree with the terms will sign the adjacent consent form in the presence of a member of the investigative team, who can also answer any questions arising during the consent process.

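### The Stroop reaction-time and Stroop HbO2 ANOVA names only alcohol-dependent and healthy control groups, so four cocaine sub-hypotheses on primary outcomes have no stated test

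*Protocol article*

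**What the plan says.** Three groups are enrolled. The Participants section states: "Twenty alcohol-dependent, 20 cocaine-dependent and 20 healthy control individuals will be recruited to take part in the study". The Study design section adds: "Alcohol-dependent, cocaine-dependent and healthy control subjects will undergo all three conditions in randomised order".

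The Background hypotheses on moderate exercise open with "In alcohol-dependent and cocaine-dependent participants, compared to a passive control condition, a bout of moderate exercise will" and go on to list, among others, "improve behavioural performance on the Stroop test" and "elicit increased activity in the prefrontal cortex during the Stroop test". The intense-exercise hypotheses are written for the same two patient groups and cover the same four outcomes. The Abstract counts inhibitory control and the haemodynamic response to the Stroop test among the primary outcomes.

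The Statistics section then sets out two ANOVAs, each group × condition × time:

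- For Stroop reaction time and the haemodynamic response to incompatible Stroop trials, the group factor is "2 (group: alcohol dependent, healthy controls".
- For cue-elicited craving and cue HbO2, the group factor again has two levels, this time unnamed, while the outcome is described as the difference between alcohol or cocaine cues and neutral cues.

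Bonferroni-corrected t tests follow any significant interaction.

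**The concern.** The first ANOVA is the only analysis the article states for the Stroop outcomes, and it spells out its group levels. The cocaine-dependent group is not one of them. The follow-up t tests do not bring it back, because they only decompose interactions found in that model. Anyone who follows the text would collect Stroop and fNIRS data from 20 cocaine-dependent people in three sessions each and have no planned test for what the Background predicts about them.

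This is more than a detail left to a fuller analysis plan. The article fixes the factor, the number of levels and their names, and these conflict with its own hypotheses. The power statement in the same section also rests on prefrontal activity and inhibitory control, so the group size of 20 was justified on the kind of outcome from which the cocaine group is left out. If the gap stays open, the handling of the cocaine group on primary outcomes could be chosen after the results are known.

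**Working it through.** **The plan's own figure.** The Statistics section gives 17 per group for 85% power at alpha 0.05, raised to 20 for drop-out. The drop-out step is consistent with an implied rate of 1 − 17/20 = 15%, since 17/(1 − 0.15) = 20. The 17 cannot be reproduced, because the article gives no numerical effect size, correlation among repeated measures or test family. The point does not depend on it.

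**Groups, side by side.**

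| Place in the article | Groups |
|---|---|
| Participants; Study design | alcohol, cocaine, healthy control (20 each, 60 in all) |
| Background, both sets of hypotheses | alcohol and cocaine |
| Statistics, Stroop ANOVA | alcohol, healthy control |
| Statistics, craving and cue ANOVA | two levels, unnamed |

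**Participants.** The Stroop ANOVA holds 2 × 20 = 40 of 60. The other 20 are 20/60 = 33% of the trial and 20/40 = 50% of the patients.

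**Hypotheses about cocaine-dependent participants.** There are 2 intensities × 4 outcomes = 8 sub-hypotheses. Two of the four outcomes are Stroop outcomes, so 2 × 2 = 4 have no stated test. The other 2 × 2 = 4 (craving and cue response) fall under the second ANOVA.

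**Possible readings of the second ANOVA.** Two levels cannot hold three separate groups in one model. The text allows:

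1. one patient-versus-control model per substance, in which nothing is pooled;
2. all patients against controls, which puts both substances in one level;
3. alcohol against cocaine, which leaves no place for the Background's expectation about healthy controls;
4. alcohol against controls, as in the Stroop model, which fits poorly with the mention of cocaine cues.

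The article does not say which is meant.

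**Questionnaire ranges.** The alcohol questionnaire has 12 items and a stated range of 12–84, which implies scoring of 1–7 per item (12 × 1 = 12, 12 × 7 = 84). The cocaine questionnaire has 10 items, also on a 7-point scale, and its section says "scores are summed to produce a final value ranging between 7 and 70". On the same scoring the range is 10 × 1 = 10 to 10 × 7 = 70, so the lower limit of 7 cannot occur. A one-point shift on every item moves the total by 12 on one questionnaire and 10 on the other. This matters only if totals from both substances enter one model.

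**Does the correction need more participants?** With separate models, cocaine versus control has the same number per group as the planned alcohol versus control model. For a three-level factor, here is an illustration using λ = f²·N·m/(1 − ρ), df1 = (k − 1)(m − 1) and df2 = (N − k)(m − 1), where k is the number of groups and m the number of measurements. I assume ρ = 0.5 and the f that gives 85% power for a two-group interaction at 17 per group.

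| m | f (assumed) | 3 groups, 17 each | 3 groups, 20 each |
|---|---|---|---|
| 2 | 0.265 | 91.7% | 95.6% |
| 3 | 0.237 | 91.8% | 95.8% |
| 6 | 0.191 | 91.6% | 95.9% |

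At the same f, 15 per group would reach 85%. The between-subject error df rises from 40 − 2 = 38 to 60 − 3 = 57.

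**The case against.** The strongest reply is that this is a drafting slip. Alcohol-only wording recurs where cocaine is plainly included: the fNIRS recordings section speaks only of alcohol cue exposure, although the cue section describes cocaine films, and one Background paragraph mentions only patients treated for alcohol addiction and healthy adults. That is a likely explanation. It does not supply the missing analysis, and the Statistics section is where a reader must look for it.

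Four stronger readings are tempting, and the article does not support them.

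- A reader might infer that the cocaine group is never analysed at all. The second ANOVA and the fNIRS recordings section both refer to cocaine cues, so the group probably enters the craving and cue analysis. The gap is shown for the Stroop outcomes only.
- A reader might infer that cocaine must be either dropped or pooled with alcohol in the second ANOVA. One model per substance is an equally natural reading, since each patient sees films of, and answers a questionnaire on, their own substance.
- It follows that mixing 12-item and 10-item totals is a risk under some readings and is nowhere stated as the plan. It is not even certain that cue-elicited craving in that sentence means questionnaire totals, because the fNIRS section uses the phrase for haemodynamic difference waveforms.
- A reader might add that controls are mismatched to the alcohol group, because "The mean age and gender distribution of the cocaine-dependent and alcohol-dependent participants combined will be used as a guide" in choosing them. The article gives no age difference between the patient groups, so no size can be put on this. The patient hypotheses compare exercise with rest within the same person, and an age difference from controls does not bias those contrasts. Covariate adjustment is a separate preference.

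**Conclusion.** The point holds for the Stroop outcomes and is an error as written. Four of the eight cocaine sub-hypotheses, all on outcomes named as primary, have no stated test, and 20 of 60 participants have no place in the only Stroop analysis given. This rests on the article's own text and on no assumed figure. For craving and cue HbO2 the defect is narrower: the two group levels are undefined for a three-group trial. The 7–70 range is a genuine but minor slip that affects no test. The power figures illustrate only that the correction need not enlarge the trial; they depend on the assumed ρ and on the same f carrying over to three groups.

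**What to change.** In the Statistics section:

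1. Include the cocaine-dependent group in the Stroop reaction-time and Stroop HbO2 analysis. Either use a three-level group factor (alcohol, cocaine, healthy control) with condition contrasts estimated within each patient group, or state separate alcohol-versus-control and cocaine-versus-control models. Either closes the gap.
2. Name the group levels of the craving and cue ANOVA in the same way.
3. State that questionnaire craving is analysed per substance, or as an item mean (1–7) if substances share a model.

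In the Craving self-report section, change the cocaine range to 10–70.

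The cost is a few sentences, with no new data. The article reports recruitment as incomplete and the conditions as unblinded, so the change should be fixed and dated before any outcome data are analysed.
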